#### Secondary outcomes and measures

The following secondary outcome measures will be assessed in all participants at 1-month, 3-months, and 6-months after enrollment: 7-day point-prevalence abstinences, 3-month continuous abstinence, reduction in the number of cigarettes smoked per day, the number of quitting attempts, and attendance to other smoking cessation services.

The 7-day point-prevalence abstinence will be measured through the question “Have you ever smoked over the past 7 days?” The measurement of 3-month continuous abstinence is identical to that of 6-month continued abstinence as explained before. The number of cigarettes smoked per day and the number of quitting attempts will be asked at each follow-up. Attendance to other smoking cessation services will be measured through the question “Have you ever used any other professional smoking cessation services? If yes, please describe them briefly.”

As the participants in this study will be smokers willing to quit within 1 month, we presume this study will mainly reveal if our APP could help smokers in the preparation stage to quit successfully. However, since not every smoker proclaiming interest in quitting will make a quit attempt by their due date [37], this study could also explore whether our APP can increase the motivation of smokers to quit smoking. Therefore, we will specifically measure how many participants in each group have made attempts to quit 1 month after enrollment to explore the efficacy of our APP in increasing the motivation to make a serious quit attempt.

For those who relapse at the follow-up points, the reduction in the number of cigarettes smoked per day, the number of quit attempts, and attendance to other smoking cessation services will be considered as secondary outcomes and will be used to compare against the baseline data.

Furthermore, APP acceptability and engagement will be measured in the intervention group 1 month after enrollment by an adopted TAM (Technology Acceptance Model) questionnaire, which involves perceived usefulness and perceived ease of use [38]. Also, the frequency and duration of each login, the utilization of each specific function, and the compliance with guidance will be recorded automatically for further analysis. The full list of measurements is presented in Table 1.

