### Outcomes and measures

#### Primary outcome and measures

As we explained before, our SSC APP includes motivational protocols for those not ready to decide on a target quit date. In this study, we intend to explore the efficacy of the SSC APP as a whole, so the follow-up in this study will be tied to the date of intervention initiation. 6-month continued abstinence is selected as the primary outcomes. Considering there is no close contact or interaction between participants and the study team, biochemical verification may be infeasible as the SRNT guidelines have suggested [35], it will be self-reported. 6-month continued abstinence will be defined using the Russell 6 Standard [36] but without biochemical verification (i.e., tolerate fewer than five incidents of smoking from the quit date) and will be measured through the question “Have you smoked at all since (date of the start of the continuous abstinence period) ? A: No, not a puff; B: 1–5 cigarettes; C: More than 5 cigarettes.”

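### The question on other cessation services has no time window, so follow-up answers mix pre-trial with in-trial use and dilute the comparison between arms

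*Protocol article*

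**What the plan says.** The protocol article, under Secondary outcomes and measures, opens its list with "The following secondary outcome measures will be assessed in all participants at 1-month, 3-months, and 6-months after enrollment". The list ends with "the number of quitting attempts, and attendance to other smoking cessation services". The instrument for the last of these is given word for word: "Have you ever used any other professional smoking cessation services", followed by "If yes, please describe them briefly". Neither part names a period or asks for a date.

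The same section adds that, for participants who relapse, "attendance to other smoking cessation services will be considered as secondary outcomes and will be used to compare against the baseline data".

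Under Exclusion criteria, only people currently following another cessation programme are kept out. Past use of a clinic or quitline is not an exclusion.

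**The concern.** The outcome is meant to describe what participants did at 1, 3 and 6 months after enrolment. A lifetime question does not do that. Once the answer is yes it stays yes, whether the service was used years before the trial or last week.

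The outcome matters to interpretation. Both arms receive the manual so that the app's own contribution can be isolated. Participants given only the manual might look for help elsewhere more often, or the app's personalised advice might lead its users towards services. Either would be relevant in explaining a difference in abstinence, or the lack of one. This is the only measure of such co-intervention described in the article's text, although the schedule in Table 1 is not visible.

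**Working it through.** **The quoted items side by side**

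| Item | Period stated |
|---|---|
| "Have you smoked at all since (date of the start of the continuous abstinence period" (Primary outcome and measures) | From a named date |
| "Have you ever smoked over the past 7 days" (Secondary outcomes and measures) | Past 7 days |
| "Have you ever used any other professional smoking cessation services" (Secondary outcomes and measures) | None |

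Of these three, only the services item has no period.

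**Plan's own figures.** There is none for this outcome. The sample size for the primary outcome reproduces closely: 13.1% versus 6.4%, two-sided 5%, 80% power gives 307 per arm by the pooled formula, against 309 stated, and 309/(1 − 0.358) = 481.3, against 481 stated. This point does not touch it.

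**Inputs for the illustration**
- n = 500 per arm (Randomization section).
- In-trial use u = 15% in one arm and 8% in the other: assumed.
- Past use q = 10% or 20%: assumed. The Introduction says nearly 90% of smokers who tried to quit in the past 12 months sought no professional help. That suggests the order of magnitude, but it is not lifetime use among enrolled participants.
- In-trial use independent of past use: assumed.

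**Formulas**
- P(ever) = q + (1 − q)u, so the difference between arms shrinks by the factor (1 − q).
- Power = Φ{[|p1 − p2|√n − 1.96√(2p̄(1 − p̄))] / √(p1(1 − p1) + p2(1 − p2))}, where p̄ is the mean of p1 and p2.

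**Step 1, anchored item.** 15% versus 8%, n = 500: (0.07 × 22.36 − 1.96 × 0.4512)/0.4484 = 1.52, power 93.6%.

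**Step 2, raw lifetime item**
- q = 10%: 0.10 + 0.90 × 0.15 = 23.5%; 0.10 + 0.90 × 0.08 = 17.2%. Difference 6.3 points, power 69.7%.
- q = 20%: 0.20 + 0.80 × 0.15 = 32.0%; 0.20 + 0.80 × 0.08 = 26.4%. Difference 5.6 points, power 49.5%.
- Share of yes answers in the lower-use arm that reflect pre-trial use only, q(1 − u)/P(ever): 0.10 × 0.92/0.172 = 53%; 0.20 × 0.92/0.264 = 70%.

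**Step 3, lifetime item also asked at baseline, counting only no-to-yes changes among never-users**
- q = 10%: 500 × 0.90 = 450 per arm, 15% versus 8%, power 91.0%.
- q = 20%: 500 × 0.80 = 400 per arm, power 87.5%.

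**Sensitivity to the assumed rates.** With in-trial use of 10% versus 5%, the anchored item has 85% power. The raw lifetime item has 48% (q = 10%) or 30% (q = 20%).

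**Sensitivity to follow-up.** If only 500 × (1 − 0.358) = 321 per arm respond, even the anchored item (15% versus 8%) has 79.5% power.

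**The case against.** A reader might infer that the item cannot measure co-intervention during the trial at all, and that comparing it with baseline tells us nothing. The documents do not support that. If a truthful lifetime answer can only move from no to yes, every such change after baseline is first use during the trial. The article plans a comparison with baseline data and collects smoking history at prescreening, so a baseline value may well exist. Step 3 shows that using it costs about 3 to 6 percentage points of power, not 24 to 44.

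This recovery has limits. The article does not state that the same item is asked at baseline. It states the baseline comparison only for participants who relapse. Renewed use by a past user stays invisible.

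The wording may also be loose translation. The 7-day item uses the same adverb, the reference to other services and the follow-up schedule suggest that in-trial use is intended, and the fielded questionnaire is not shown. This is a fair caution, but the 7-day item adds an explicit window and the services item does not. The free-text description might reveal timing in some cases, but it asks for no dates.

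It might also be inferred that the trial's main result is biased. It is not. Past use should balance between arms by randomisation, the analysis follows intention to treat, and use of other services after allocation bears on interpretation, not on the validity of the randomised comparison. Nor is the trial powered for this outcome, so the power figures only show the scale of dilution.

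**Conclusion.** The point holds as a minor measurement defect in one secondary outcome. As printed, the question mixes use before enrolment with use during the trial. Under the assumed rates, the difference between arms shrinks from 7.0 points to 6.3 or 5.6, and more than half of the yes answers in the lower-use arm would concern pre-trial use only. Power for the raw comparison falls from about 94% to about 70% or 49%. If new use among baseline never-users is analysed instead, it falls only to about 91% or 88%. All the usage rates, and the independence of past and in-trial use, are assumptions. The conclusion that the item lacks a window and admits past users rests on the text alone. The primary outcome and the sample size are unaffected.

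**What to change.** At each follow-up, ask about professional cessation services used *since you joined this study* (first follow-up) or *since your last questionnaire* (later ones). Ask about lifetime use at baseline only. State that in-trial use is compared between arms in all randomised participants, consistent with the article's own plan to assess the outcome in everyone, and not only against baseline in those who relapse. If the fielded questionnaire already carries such a window, correcting the printed wording is enough.

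The cost is one reworded item before launch, and one baseline item if lifetime use is not already asked there. It adds no visit and no participants. If data collection has already begun with the lifetime wording and a matching baseline item exists, the fallback is to analyse no-to-yes changes among baseline never-users in both arms and to report that renewed use by past users was not captured.

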### Sample size and power calculation

The proposed sample size is based on the primary outcome of self-reported 6-month continuous abstinence. Based on a meta-analysis conducted by Ybarra [26], the 6-month continuous abstinence for mobile phone-based smoking cessation intervention is 13.1%, compared with 6.4% in the control group. To detect a 2-sided significant difference between groups with a power of 80% and significance level of 5%, 309 participants in each arm are estimated to be required. Considering a 35.8% loss to follow-up in one study concerning SSC APP conducted in China [27], the final minimum sample size is 481 per group. Eventually, we set a target sample size at 1,000 people to cover the minimum sample size.

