### Statistical analysis

Upon completion of data collection, data will be cleaned and prepared for data analysis. Primary and secondary outcome variables will be checked for distribution, outliers, and missing patterns, and appropriate steps will be taken where necessary. All analysis will be conducted through SAS 9.4. Baseline demographics and smoking-related characteristics will be summarized and presented. Continuous variables (e.g. age) will be presented as numbers observed, means, and standard deviations. Categorical variables (e.g. marital status) will be presented as frequencies and percentages.

The main analysis will be focused on the comparison of smoking cessation rates in the intervention and control groups. This involves a comparison of the primary outcome variables and some secondary outcome variables including 7-day point-prevalence abstinence and self-reported continuous abstinence at each follow-up point. Independent t-tests and χ^2^ tests will be used to detect differences between the two groups depending on the type of variables. Logistic regression will be explored to assess group differences after adjusting for any baseline demographic or clinical characteristics that showed significant differences and variables that have been reported to be associated with smoking cessation [39].

Our analysis will be conducted based on intention-to-treat (ITT) principle and participants who are lost to follow-ups will be considered as continuing smokers with no reduction in cigarette consumption compared with baseline. The results from the analysis using the Multiple Imputation and Last Observation Carried Forward approaches to process missing data and per-protocol analysis will be conducted as sensitivity analyses. Subgroup analysis by baseline characteristics on quitting outcomes will be conducted by interaction terms.

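### Cigarette reduction, quit attempts and use of other services are given two incompatible populations and comparators, one of which is not protected by randomisation

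*Protocol article*

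**What the plan says.** All three outcomes appear in the first paragraph of Secondary outcomes and measures, which opens: "The following secondary outcome measures will be assessed in all participants", at 1, 3 and 6 months. The third paragraph adds a count, in each group, of participants who have attempted to quit by 1 month.

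The fourth paragraph returns to the same three outcomes with a different population, "For those who relapse at the follow-up points, the reduction in the number of cigarettes smoked per day", and continues through quit attempts and other services to the statement that they "will be considered as secondary outcomes and will be used to compare against the baseline data". The text shown does not define relapse.

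The Statistical analysis section names the primary outcome, 7-day point-prevalence abstinence and continuous abstinence for the main between-group comparison. It plans t-tests and χ² tests between groups according to variable type. It states intention-to-treat, with participants lost to follow-up treated as "continuing smokers with no reduction in cigarette consumption compared with baseline". It does not say which population or comparator applies to cigarette reduction, quit attempts or use of other services.

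The Abstract lists cigarette reduction and recent quit attempts among the main secondary outcomes.

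**The concern.** The fourth paragraph changes two things at once: who is analysed, and what they are compared with.

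- **Population.** Whether a participant is smoking at follow-up is decided after randomisation and is what the APP is meant to influence. If the APP produces more quitters, the smokers left in the two arms are no longer comparable, and a contrast between them is not protected by randomisation.
- **Comparator.** Everyone enrolled intends to quit within 1 month (Inclusion criteria), so some improvement on baseline is expected in both arms. A before-after change within an arm does not estimate the effect of the APP.

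With both versions in the protocol, the choice could be made after results are seen, for outcomes that the Abstract ranks among the main secondary ones.

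**Working it through.** **The plan's own figure.** No power or effect size is stated for these outcomes. The only figure is the primary sample size: "the 6-month continuous abstinence for mobile phone-based smoking cessation intervention is 13.1%, compared with 6.4% in the control group", two-sided 5%, 80% power, "309 participants in each arm are estimated to be required". The pooled two-proportion formula, with mean rate 0.0975 and difference 0.067, gives

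n = [1.960·√(2·0.0975·0.9025) + 0.8416·√(0.131·0.869 + 0.064·0.936)]² / 0.067² = 307 per arm.

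The stated 309 is close. Allowing for 35.8% loss, 309/(1 − 0.358) = 481.3, against the stated 481. The figure reproduces, and the point does not depend on it.

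**Size of the subset.** If relapsers are taken as all non-abstainers, 500 per arm at the design rates leaves 500 × 0.869 = 434.5 (APP) and 500 × 0.936 = 468 (control). So 0.067/0.936 = 7.2% of the people in the control subset have counterparts in the APP arm who left it by quitting.

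**Cigarettes per day.** Assumptions not in the documents: mean baseline 15/day; people who would smoke under either arm cut 3/day; the APP's only effect is to add quitters; follow-up is complete. Let r be the reduction that the extra quitters would have made under control.

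- Non-abstainers: APP mean = 3; control mean = (0.869·3 + 0.067·r)/0.936.
- All randomised, abstainers at zero: APP minus control = 0.067·(15 − r).

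| r (per day) | Non-abstainers, APP − control | All randomised, APP − control |
|---|---|---|
| 3 | 0.00 | +0.80 |
| 6 | −0.22 | +0.60 |
| 8 | −0.36 | +0.47 |
| 10 | −0.50 | +0.34 |
| 12 | −0.64 | +0.20 |

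A simulation of 2 million participants (assumed baseline mean 15, SD 7; mean fractional reduction 0.2) varied the correlation between propensity to quit and cutting down. At correlations of 0, 0.3, 0.5 and 0.7 the non-abstainer difference was 0.00, −0.13, −0.21 and −0.29. The all-randomised difference was +0.81, +0.71, +0.64 and +0.58.

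**Quit attempts.** Every abstainer has made at least one attempt. Suppose the same share a attempts in both arms, and again take relapsers as non-abstainers. The share of non-abstainers with an attempt is (a − 13.1)/86.9 for APP and (a − 6.4)/93.6 for control, in per cent.

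| a (assumed) | APP | Control | Difference (points) |
|---|---|---|---|
| 40% | 26.9/86.9 = 31.0% | 33.6/93.6 = 35.9% | −4.9 |
| 60% | 46.9/86.9 = 54.0% | 53.6/93.6 = 57.3% | −3.3 |
| 80% | 66.9/86.9 = 77.0% | 73.6/93.6 = 78.6% | −1.6 |

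The APP changed nobody's attempts in this example. The deficit arises only from removing more successful attempters from its arm.

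**If relapse requires an earlier quit.** Never-quitters then leave the set, and the cigarette results above no longer apply; an APP that prompts more attempts changes the set in another way. If an earlier quit counts as an attempt, everyone in the set has one, and the share with an attempt carries no information.

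**The case against.** The strongest reply is that the plan already analyses everyone. The first paragraph covers all participants, 1-month attempts are counted in each group, and the Statistical analysis section has intention-to-treat and between-group tests. The fourth paragraph may only add a summary for those still smoking, and its reference to baseline may only define the change score. This is a fair reading, and it rules out a stronger one: a reader might infer that these outcomes are restricted to relapsers, but the text does not settle that. Nor does it settle the opposite. The fourth paragraph is the most specific statement about these outcomes, and the general sentence on tests names no population.

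A reader might also infer that the rule for losses contradicts a relapser set. It does not: people counted as continuing smokers with zero reduction could sit inside a non-abstinent set. The conflict is with analysing all randomised participants.

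The illustrations have limits, and these stand. The inputs are assumed and losses are left out. The cigarette reversal needs the extra quitters to be people who would otherwise have cut down more than average; with no such link the difference is zero. It may also be small against sampling error. If the SD of reduction were about 3.2/day (assumed), the standard error would be 3.2·√(1/434.5 + 1/468) = 0.21, similar to the middle of the simulated range.

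Finally, the all-randomised gain in these examples comes wholly from extra quitters coded as zero. It partly restates abstinence and does not isolate cutting down among continuing smokers.

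**Conclusion.** The point holds as an unresolved contradiction over population and comparator for three secondary outcomes. It is more than detail left to an analysis plan, because both statements stand in the same section and conflict.

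The resulting bias is possible, not certain. With relapsers taken as non-abstainers and the assumptions above, it runs from 0 to about 0.6 cigarettes/day against the APP, while the all-randomised difference is about 0.2 to 0.8 in its favour. For having made a quit attempt, the false deficit is about 4.9 to 1.6 percentage points if 40% to 80% attempt in both arms.

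A reader might infer that the relapser analysis must work against the APP. The documents do not support that: they leave relapse undefined and give nothing on how quitting and cutting down are related, so the direction could differ. The primary outcome and sample size are unaffected. The wording should be corrected, but the trial's main conclusion does not depend on it.

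**What to change.** Reconcile the first and fourth paragraphs of Secondary outcomes and measures:

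- Compare cigarettes per day, quit attempts and use of other services between arms in all randomised participants.
- Count abstainers as zero cigarettes per day, adjust the change in cigarettes per day for its baseline value, and handle losses by the rule already in the Statistical analysis section.
- Keep any relapser-only or versus-baseline summary as descriptive, without a test, and define relapse if the term stays.

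The cost is wording only, since the outcomes are already to be collected from everyone. The small downside is that the all-randomised cigarette outcome partly reflects abstinence; the descriptive summary can show cutting down among those still smoking.

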**Table 1 Tab1:**
[figure not shown]
Schedule of enrollment and follow-up assessments

^a^ Schedule of enrollment and follow-up assessments

^b^ FTND, fagerström test of nicotine dependence

### Procedures

Figure 2 shows the trial flow chart. Eligibility will be assessed at baseline and eligible participants will be allocated to either the intervention or control group in a ratio of 1:1 after stratification. Participants in both groups will receive self-help materials and the participants in the intervention group will receive the SSC APP in addition. Then participants in both groups will be followed up  for 6 months after enrollment.

**Fig. 2 Fig2:**
[figure not shown]
Trial flow diagram

### Statistical analysis

Upon completion of data collection, data will be cleaned and prepared for data analysis. Primary and secondary outcome variables will be checked for distribution, outliers, and missing patterns, and appropriate steps will be taken where necessary. All analysis will be conducted through SAS 9.4. Baseline demographics and smoking-related characteristics will be summarized and presented. Continuous variables (e.g. age) will be presented as numbers observed, means, and standard deviations. Categorical variables (e.g. marital status) will be presented as frequencies and percentages.

The main analysis will be focused on the comparison of smoking cessation rates in the intervention and control groups. This involves a comparison of the primary outcome variables and some secondary outcome variables including 7-day point-prevalence abstinence and self-reported continuous abstinence at each follow-up point. Independent t-tests and χ^2^ tests will be used to detect differences between the two groups depending on the type of variables. Logistic regression will be explored to assess group differences after adjusting for any baseline demographic or clinical characteristics that showed significant differences and variables that have been reported to be associated with smoking cessation [39].

Our analysis will be conducted based on intention-to-treat (ITT) principle and participants who are lost to follow-ups will be considered as continuing smokers with no reduction in cigarette consumption compared with baseline. The results from the analysis using the Multiple Imputation and Last Observation Carried Forward approaches to process missing data and per-protocol analysis will be conducted as sensitivity analyses. Subgroup analysis by baseline characteristics on quitting outcomes will be conducted by interaction terms.

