### Randomization, allocation concealment and blinding

After enrollment, eligible participants will be assigned to either the control group or intervention group in a ratio of 1:1 (500 in each). Two stratification factors, each at two levels, will be used: age (≤ 40 years, > 40) and daily cigarette consumption (≤ 20 pack-years, > 20). A random permuted block sizes of 2, 4, or 6 will be used to achieve similar numbers of participants in both the intervention group and the control group.

Allocation concealment can be guaranteed as the random number sequence will be generated by a biostatistician who is not a member of the research team, and the random number sequence will be kept secret from researchers who are responsible for the recruitment.

As the interventions in two groups cannot be completely blinded in this study, this RCT will be single-blind in which all outcome assessors and data analysts will be blind to group allocation.

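### The named group tests leave out the randomisation strata and use the baseline cigarette count inefficiently; they are valid, and the loss is small but costs nothing to avoid

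*Protocol article*

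**What the plan says.** Under Randomization, allocation concealment and blinding, the article states that "Two stratification factors, each at two levels, will be used": "age (≤ 40 years, > 40) and daily cigarette consumption (≤ 20 pack-years, > 20". Within strata, "A random permuted block sizes of 2, 4, or 6 will be used".

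Under Statistical analysis, "The main analysis will be focused on the comparison of smoking cessation rates in the intervention and control groups". Independent t-tests and chi-square "tests will be used to detect differences between the two groups depending on the type of variables". A second, adjusted analysis follows: "Logistic regression will be explored to assess group differences after adjusting for any baseline demographic or clinical characteristics that showed significant differences", together with "variables that have been reported to be associated with smoking cessation". Age group and consumption are not named there.

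Under Secondary outcomes and measures, "The number of cigarettes smoked per day and the number of quitting attempts will be asked at each follow-up", and the reduction in cigarettes per day is listed as a secondary outcome. Under Statistical analysis, participants lost to follow-up count as smokers with no reduction from baseline.

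**The concern.** When randomisation balances a prognostic factor by design, a test that omits the factor uses a standard error that is slightly too large. The result is a mildly conservative test and a little lost power. Here the factors were thought important enough to stratify on, yet no analysis is committed to using them.

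The exploratory logistic regression does not close the gap. One of its two covariate rules picks characteristics that differ significantly at baseline, and the stratified blocks all but rule that out for the stratification factors. The other rule could bring in age and consumption, but it names neither.

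For cigarettes per day, a change score implicitly gives the baseline count a slope of 1. ANCOVA estimates the slope, so it is at least as precise in a trial of this size. What is at stake is precision, not validity.

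**Working it through.** **1. The plan's own figure.** Inputs from Sample size and power calculation: 13.1% against 6.4%, two-sided 5%, power 80%. With the mean rate 0.0975,

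n = [1.960·√(2·0.0975·0.9025) + 0.8416·√(0.131·0.869 + 0.064·0.936)]² / 0.067² = (0.8222 + 0.3508)² / 0.004489 ≈ 306.5, so 307 per arm (stated: 309).

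For loss, 309 / (1 − 0.358) = 481.3 (stated: 481). The sample size therefore matches the plain two-proportion test and does not depend on adjustment.

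**2. Can the baseline-significance rule select a stratification factor?** With blocks of at most 6, the arms differ by at most 3 within a stratum, so by at most 6 at a factor level made up of two strata. If a level holds 500 of 1,000 participants (assumption), the worst split is 253 against 247. Then z = (0.506 − 0.494) / √(2·0.25/500) = 0.012/0.0316 = 0.38. The dichotomised factor cannot reach significance. In 2,000 simulated trials with four roughly equal strata it never did.

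**3. Abstinence: plain chi-square against stratified Cochran-Mantel-Haenszel (CMH) test.** The article gives no stratum effects, so the following are assumptions: 40% in one age group, 30% heavy smokers, and a range of odds ratios (OR). Overall rates are 6.4% in both arms under the null and 6.4% against 13.1% under the alternative. Blocks of 2, 4 or 6 within four strata, 6,000 runs per cell. Entries are plain / CMH, in %.

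| OR age, OR heavy smoking | Type I error, N=1,000 | Power, N=1,000 | Power, N=618 |
|---|---|---|---|
| 1, 1 | 4.52 / 4.52 | 95.23 / 95.23 | 81.13 / 81.02 |
| 1.3, 0.7 | 4.82 / 4.83 | 95.30 / 95.32 | 80.58 / 80.62 |
| 1.5, 0.5 | 4.73 / 4.85 | 94.60 / 94.75 | 81.53 / 81.77 |
| 2, 0.33 | 4.75 / 4.90 | 95.47 / 95.77 | 82.30 / 82.82 |
| 3, 0.2 | 4.67 / 5.03 | 95.65 / 96.05 | 81.68 / 83.07 |

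The simulation error of one type I entry is √(0.05·0.95/6000) ≈ 0.28 points. Both tests see the same simulated trials, so their difference is more reliable than either value alone. With stratum quit rates of 18, 5, 10 and 2% (assumption; 20,000 runs, N = 1,000), the plain test gave 4.5 to 4.6% and CMH 5.0%.

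The power gain is 0 to 0.4 points at N = 1,000. At N = 618 (2 × 309) it reaches 1.4 points, only under the most extreme effects.

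**4. Cigarettes per day: ANCOVA against a t-test on change.** With complete data and equal SDs the variance ratio is (1 + ρ)/2, which is 0.75 at ρ = 0.5 and 0.85 at ρ = 0.7. The plan's missing-data rule alters this. Let r = 1 − 0.358 = 0.642 be the responding share, ρ the responders' baseline-to-follow-up correlation and δ their mean fall in SD units. Change is zero for everyone else. In units of the baseline variance, with loss unrelated to the baseline count:

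- Var(change) = 2r(1 − ρ) + r(1 − r)δ²
- Cov(change, baseline) = −r(1 − ρ)
- Ratio = 1 − Cov²/Var = 1 − r(1 − ρ)² / [2(1 − ρ) + (1 − r)δ²]

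| ρ | δ | Ratio | Variance saved |
|---|---|---|---|
| 0.5 | 0 | 1 − 0.1605/1.000 = 0.84 | 16% |
| 0.5 | 1 | 1 − 0.1605/1.358 = 0.88 | 12% |
| 0.7 | 0 | 1 − 0.0578/0.600 = 0.90 | 10% |
| 0.7 | 1 | 1 − 0.0578/0.958 = 0.94 | 6% |

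**The case against.** The strongest reply is that a prespecified unadjusted chi-square test is valid, agrees with the sample size calculation, and gives up almost nothing. That stands, and it is why the point is minor. It is also fair that covariate detail is often left to an analysis plan, which is not shown here. But this article does name its tests, so the remark concerns a stated method rather than a gap. The adjusted logistic regression also counts in the plan's favour, because known predictors of cessation could well include age and consumption. It remains exploratory, with its covariates open.

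Three stronger readings are tempting, and the documents do not support them:

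- **That the main comparisons ignore the baseline cigarette count.** The main analysis compares cessation rates, which are binary. Cigarette reduction is secondary, and a reduction already uses the baseline count, only less efficiently.
- **That the plan prescribes a t-test on change.** It assigns tests by type of variable and promises to check distributions. The t-test on change is the natural inference, not a statement.
- **That ANCOVA would save 25% of the variance, like 1/0.75 = 1.33 times the participants.** That figure assumes complete data at ρ = 0.5. Setting lost participants to no reduction ties their follow-up to their baseline and shrinks the gain.

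**Conclusion.** The point holds as a minor one about efficiency. No analysis is committed to the stratification factors, although the design balances them. For abstinence the plain test is valid and slightly conservative (about 4.5 to 4.8% type I error), and stratifying adds about 0 to 0.4 power points at N = 1,000. A reader might infer that the primary result would be unreliable; the figures give no ground for that.

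For reduction in cigarettes per day, ANCOVA would save about 6 to 16% of the variance compared with a t-test on change. This rests on an assumed responder correlation of 0.5 to 0.7, a mean fall of 0 to 1 SD, equal SDs, 35.8% loss unrelated to the baseline count, and all randomised participants being analysed. The article gives neither the correlation nor the stratum effects.

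**What to change.** - **Reconcile the consumption factor first.** The randomisation section calls it daily consumption but gives its cut-off in pack-years, which is a different measure. The factor cannot enter a model until its definition is settled.
- **Primary abstinence test.** Use a Cochran-Mantel-Haenszel test stratified by the two factors, or a logistic regression with arm and the two factors as fixed terms. Report a risk difference with its 95% confidence interval.
- **Cigarettes per day.** Use ANCOVA on the follow-up count, with baseline count and age group as covariates.
- **Plain chi-square and t-tests.** Keep them as supportive analyses.

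The cost is a change of wording and of SAS code. No extra participant, visit or question is needed, because the baseline data are already collected.
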